**Discussion:**

This study protocol presents a RCT in which the efficacy of an integrated treatment for comorbid PTSD and SUD, Seeking Safety, is evaluated in a SUD outpatient population compared to CBT. It is expected that the intervention group will show significantly more improvement in substance use severity compared to the control group at end-of-treatment and at follow-up. Furthermore, a lower drop-out rate is expected for the intervention group. If the intervention proves to be effective, it can be implemented. A cost-effectiveness analysis will be conducted to evaluate the two treatments.

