#### Randomization

Randomization will be at patient level. The participants will be randomly appointed to either the control group or the experimental group. The care-takers are blind for this randomization. Envelopes will be distributed to the treatment facility and these contain the questionnaires that will be administered at t = 0. After completing the questionnaires patients will be randomized based on a predefined randomization schedule. Randomization will be performed in blocks of 4 and 8 (in random order). The research assistants that administer the questionnaires for t = 1 and t = 2 will be kept blind for this randomization.

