### Sample size calculation

The sample size for this study is calculated using a significance level of 95% (p < 0.05), a power of 80% and the same number of patients in the intervention and control group (ratio = 1).

Primary outcome variable is substance use severity as measured with the EuropASI. In recent studies, conducted within the same institution [34] but with a population of inpatients, a mean baseline score of 5.2 was found for the alcohol domain and 4.0 for the drugs domain. We expect the mean baseline scores for the outpatients to be somewhat lower, however not considerably. For comparison of baseline scores on the EuropASI, see [22,23]. For practical reasons we are using the mean of both domains (alcohol and drugs) for the sample size calculation. Thus, the mean score for substance use severity will be somewhat lower than (5.2 + 4.0)/2 = 4.6 with a standard deviation of 2.7. For this sample size calculation we will use a baseline score of 4.0 with the same standard deviation. We expect the substance use severity to improve with 60% [23] to 1.6 (SD = 2.0) at end-of-treatment for the intervention group and 2.8 (SD = 2.0) for the control group. We used PS – Power and Sample Size Calculation to calculate the sample size, which resulted in a sample size of 45 patients in each group. Drop-out rates for this treatment are available for the past years from a management information system and are estimated around 20%. This drop-out rate may seem low compared to the numbers that are known from previous studies in SUD patients. However, we will use this percentage to calculate the number of patients that are needed, but will perform an analysis on drop-out halfway through the study. When the drop-out rates turn out to be higher than expected, an amendment will be proposed to the medical ethical committee to continue including patients for an extended period of time. Because of the calculated drop-out rate, an extra 9 participants will be included in both the intervention and the control group, yielding a total of 108 participants for the randomized controlled trial. Based on treatment entry numbers from previous years, approximately two years will be needed to include all patients. Furthermore, this number of patients seems plausible considering sample sizes in previous studies that show similarity in design [21,22].

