### Instruments and outcome

The primary outcome in this study is substance use severity at end of treatment as measured with the EuropASI. This measure will provide a composite score for alcohol and drugs which incorporates the number of days of use in the previous 30 days, amount of money spent on drugs or alcohol, perceived problems and burden of problems associated with substance use. The composite score for alcohol use severity will be used as the primary outcome measure for patients with alcohol use disorder and the composite score for drug use severity will be used for patients with substance use disorder according to the DSM-IV. Secondary outcome measures are the other measures listed below.

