### Statistical analyses

All analyses will be executed using SPPS for Windows version 18.0. Frequency tables will be provided for all baseline, end of treatment and follow-up variables. Descriptive statistics will include mean, median, interquartile range, numbers and percentages of patients, as appropriate. If applicable, 95% confidence intervals will be given. To compare differences between groups (Seeking Safety vs CBT) *t*-test or mann whitney U tests will be used in case of continuous variables, as appropriate. For categorical variables chi-squared tests will be used. Repeated measures analyses (mixed models in SPSS) will be used to test the differences between the treatment conditions over time in severity of substance use problems as measured by the EuropASI severity score (pre, post and follow-up). The data will be tested for normality and transformed as appropriate when the data are skewed. Analyses will be based on the intent-to-treat principle. Participants have to attend at least one session to be considered part of this group. Differences regarding gender will be analysed and when appropriate, gender will be included in the analyses as a confounder or effect modifier. Multiple Imputation will be used for missing data. Effect sizes will be calculated to facilitate comparison of improvement between the two groups. Linear regression analyses will be used to determine the predictors of change in substance use and trauma symptoms. Also, amount of prior psychiatric treatment will be used in the analysis as a covariate.

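### The set called intent-to-treat leaves out randomised patients who attend no session, which contradicts the stated principle and can bias the primary comparison in either direction

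*Protocol article*

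**What the plan says.** Two adjacent sentences in the protocol article, Statistical analyses, fix the analysis set. The first is "Analyses will be based on the intent-to-treat principle". The second is "Participants have to attend at least one session to be considered part of this group". The most natural reading of the second is that it defines who belongs to the intent-to-treat group. The section ties the rule to no single endpoint and describes no other analysis set. It also plans multiple imputation for missing data.

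The Randomization section gives the order of events: "Randomization will be at patient level", and "After completing the questionnaires patients will be randomized based on a predefined randomization schedule". On blinding it says "The care-takers are blind for this randomization", and it keeps the research assistants at t = 1 and t = 2 blind. It does not say when patients learn their allocation.

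The primary endpoint is set under Instruments and outcome: "The primary outcome in this study is substance use severity at end of treatment as measured with the EuropASI". Drop-out is listed for assessment under Aims, and the abstract predicts a direction: "Furthermore, a lower drop-out rate is expected for the intervention group".

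**The concern.** Whether a patient turns up to a first session is settled after randomisation. Once attendance decides who is analysed, the two groups are no longer those that randomisation made comparable. The label intent-to-treat tells readers that this protection is in place when it is not.

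The plan gives no reason to treat non-start as independent of arm. It predicts a difference in drop-out, and both the Background and the Discussion suggest that cultural differences may affect how Dutch patients adhere to Seeking Safety.

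The stake is mainly the primary comparison. The cost-effectiveness analysis uses the primary outcome as its effect measure, so any bias would carry over. If the same set also served for drop-out, the earliest drop-outs would be removed from an outcome on which the trial has a stated expectation. They would also be missing from the halfway drop-out check that can lead to extended recruitment (Sample size calculation).

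**Working it through.** **1. Order of events.** Baseline questionnaires, then randomisation, then the first session. Every randomised patient therefore has baseline data, and attendance comes after allocation. Multiple imputation cannot bring back patients who are outside the set being imputed.

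**2. The plan's own figure.** Inputs from Sample size calculation: end-of-treatment means of 1.6 and 2.8 (difference 1.2), SD 2.0, 5% significance (taken as two-sided, since sidedness is not stated), 80% power. The normal approximation is 2 × (1.960 + 0.842)² × 2.0² / 1.2² = 43.6. The t-test version gives 44.6, rounded up to 45, which matches the article. Adding 9 gives 54 per group and 108 in total.

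**3. Size of the bias (assumed inputs).** The article gives no non-start rate, so rates are assumed. Suppose there is no true effect, both arms have a mean of 2.8 over all randomised patients, and non-starters score g points worse than starters. With non-start fraction f, the mean among starters is 2.8 − f × g. Take g = 1.0 (0.5 SD) or g = 2.0 (1.0 SD), 54 randomised per arm, and outcomes available for all starters.

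| Non-start, arm A / arm B | g | Starters' means, A / B | Spurious difference | Share of 1.2 | Two-sided type I error |
|---|---|---|---|---|---|
| 10% / 10% | 1.0 or 2.0 | equal | 0 | 0% | 5.0% |
| 5% / 15% | 1.0 | 2.75 / 2.65 | 0.10 | 8% | 5.7% |
| 5% / 15% | 2.0 | 2.70 / 2.50 | 0.20 | 17% | 7.8% |
| 0% / 20% | 1.0 | 2.80 / 2.60 | 0.20 | 17% | 7.8% |
| 0% / 20% | 2.0 | 2.80 / 2.40 | 0.40 | 33% | 16.5% |

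The type I error uses the standard error of the difference. For 5% / 15% this is 2.0 × √(1/51.3 + 1/45.9) = 0.406, where 51.3 = 54 × 0.95 and 45.9 = 54 × 0.85. Lower scores are better, so arm B, with more non-starters, looks better. If non-starters had the better prognosis, the sign would reverse. Equal rates with different kinds of non-starter would also bias the result.

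**4. Drop-out, if the same set were used.** Suppose true drop-out is 20% in both arms, of which never-starting accounts for 15 percentage points in one arm and 5 in the other. The restricted set shows (0.20 − 0.15)/(1 − 0.15) = 5.9% and (0.20 − 0.05)/(1 − 0.05) = 15.8%. The arm that lost more patients before the first session appears to retain them better.

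**5. Price of analysing everyone.** Suppose never-starters gain no relative benefit, the non-start rate f is the same in both arms, the SD stays at 2.0 and all 54 per arm contribute. The difference becomes 1.2 × (1 − f).

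| Non-start | Difference | Power with 54 per arm | Needed per arm for 80% |
|---|---|---|---|
| 5% | 1.14 | 84.2% | 49 |
| 10% | 1.08 | 80.1% | 54 |
| 15% | 1.02 | 75.5% | 61 |
| 20% | 0.96 | 70.3% | 69 |

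**The case against.** The best defence is that the rule is pre-specified and openly stated, and may do no harm. Baseline is placed at the start of treatment, so the gap between randomisation and the first session may be short. Both arms are weekly closed groups of the same length. If patients learned their arm only on arrival, non-start could not depend on it. The planned mixed model uses baseline scores and may absorb part of any prognostic difference. At 5% versus 15% non-start, the inflation of type I error is modest.

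Much of this stands as a limit on size. It does not remove the contradiction, because the article never says that allocation is concealed from patients until the first session. The baseline score also captures only part of prognosis.

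Some stronger readings are tempting but unsupported:

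- **That patients must know their arm before starting.** This is plausible, but the article is silent.
- **That the exclusions come on top of the 20% drop-out allowance.** That estimate is not split into never-started and left later, so it may already include never-starters.
- **That the drop-out comparison is certainly affected.** No analysis set is named for drop-out. The link is an inference from the general wording of Statistical analyses.
- **That the rule favours Seeking Safety.** If non-starters have the worse prognosis, more of them in the CBT arm would bias the result against Seeking Safety.

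It is also fair to say that the remedy is not free. Never-starters' outcomes imputed from attenders in the same arm would largely reproduce the attenders' result. The gain depends on following never-starters up.

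**Conclusion.** The point holds. As written, the primary analysis set is a modified intent-to-treat set conditioned on a post-randomisation event. It contradicts the principle stated in the sentence before it, and no analysis of all randomised patients stands beside it.

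The consequence is a possible bias of unknown size and direction, not a demonstrated one. Under the assumed 5% versus 15% non-start, with non-starters 0.5 to 1.0 SD worse, it amounts to 0.10 to 0.20 points on the scale used for the sample size. It vanishes if neither the rate of non-start nor the kind of non-starter depends on arm. An effect on the drop-out comparison follows only if the same set is used there.

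**What to change.** Replace the one-session sentence with a definition of the primary set as all randomised patients, analysed in the arm to which they were allocated, regardless of attendance. In addition:

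- Invite never-starters to the t = 1 and t = 2 assessments on the same schedule as everyone else.
- Report non-start by arm and count it as drop-out.
- Keep the at-least-one-session set as a secondary analysis, labelled modified intent-to-treat.

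The change of text is small: baseline data exist for everyone randomised and imputation is already planned. The real costs are the effort of following never-starters, more outcomes to impute where that fails, and a diluted effect. Dilution is minor at low non-start, but above about 10% it takes power below 80% under the assumptions of step 5. The halfway drop-out check is a natural place to look at the non-start rate in both arms combined.

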### Cost-effectiveness analysis

To make a comparison between the two treatments, the cost of these treatments (total costs of staff and materials) will be related to the benefits of the treatment by performing a cost-effectiveness analysis. A cost-effectiveness analysis requires a numerical estimate of the magnitude of the effects of an intervention on health outcomes. The primary outcome measure of this study will be used for this purpose. Cost will be divided by effects to calculate the cost-effectiveness ratio (C/E). The statistics of interest in the economic evaluation of health care interventions is the incremental cost-effectiveness ratio, which is defined as the difference in cost between Seeking Safety and CBT. To quantify uncertainty in the estimated incremental cost-effectiveness ratio, confidence intervals will be calculated. In addition, a special variant of economic analysis is planned, i.e., cost-utility analysis, to incorporate the preferences (utilities) of the participants considering their own health status at the start of treatment and after follow-up. Based on these preferences combined with life expectancy figures, calculation of so-called QALYs is applicable. A general measure to express the benefits of the two different treatment strategies will be calculated by subtracting the number of quality-adjusted life years computed after follow-up from the number of QALYs computed at baseline. Subsequently, quality-adjusted life years can be combined with the cost of each treatment strategy to arrive at the cost per QALY gained [48,50].

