## Methods

### Study design

For this study a randomized controlled design is used. Semi-structured interviews and self-report questionnaires will be used to measure change over time on variables at three time points: at the start of the treatment (t = 0), at end of the treatment (t = 1) and three months after the end of treatment (follow-up, t = 2). These points in time are chosen to conform to standard evaluation procedures within our facility. Routine outcome monitoring is conducted at completion of treatment for the outpatients or at three months after the start of treatment. The administration of questionnaires for the study will be synchronized with this monitoring. Both Seeking Safety and CBT will consist of weekly group sessions of 1 3/4 hours for 12 weeks (12 sessions total). This design keeps dosage equivalent across the treatment conditions, and has been used successfully in a prior recent RCT of Seeking Safety [21]. Both Seeking Safety and CBT will be offered in closed-group format, as this is the standard in the control condition. Participants will not be financially rewarded for their participation. The results of the study will be presented following the CONSORT guidelines [33].

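### The incremental cost-effectiveness ratio is defined as the cost difference alone; the difference in effect is missing from the denominator

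*Protocol article*

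**What the plan says.** Under Aims, the protocol article names a cost-effectiveness comparison of the two treatments as its second aim. The section Cost-effectiveness analysis sets out the method:

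- Costs and benefits are to be linked: "the cost of these treatments (total costs of staff and materials) will be related to the benefits of the treatment".
- The effect measure is fixed: "The primary outcome measure of this study will be used for this purpose".
- A simple ratio comes first: "Cost will be divided by effects to calculate the cost-effectiveness ratio (C/E").
- The main statistic is then named, "The statistics of interest in the economic evaluation of health care interventions is the incremental cost-effectiveness ratio", and described as "the incremental cost-effectiveness ratio, which is defined as the difference in cost between Seeking Safety and CBT".
- Uncertainty follows: "To quantify uncertainty in the estimated incremental cost-effectiveness ratio, confidence intervals will be calculated".
- A cost-utility analysis is added, in which "quality-adjusted life years can be combined with the cost of each treatment strategy to arrive at the cost per QALY gained".

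Neither this section nor any other part of the article mentions a difference in effect between the arms as part of the ICER.

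**The concern.** An ICER is the extra cost of one treatment over another per extra unit of effect. It needs two between-arm differences, one in cost and one in effect. The article gives only the first. A difference in cost is not a ratio, and it cannot show whether any extra money buys anything.

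This is a definition that is stated, and stated wrongly. It is not a detail left to a fuller document. It concerns the statistic that the article itself singles out for its second aim, and Implications for practice says that the cost-effectiveness results are meant to inform policy makers. If the sentence were applied literally, the reported figure would not respond to the trial's clinical result.

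**Working it through.** The article reports no ICER, no cost and no willingness-to-pay value, so there is no figure to reproduce. The check is of the definition, first in symbols and then with an illustration.

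**In symbols.** Let C be mean cost per patient and E be mean improvement on the primary outcome, for Seeking Safety (SS) and CBT.

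- As defined in the article: C_SS − C_CBT.
- The ICER: (C_SS − C_CBT) / (E_SS − E_CBT).
- The simple ratio, read per arm: C_SS / E_SS and C_CBT / E_CBT.

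E does not appear in the first expression, so no result on effect can change it.

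**Inputs for the illustration.**

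- Costs are assumed: 1000 units for CBT, and 1000, 1050 or 1200 for Seeking Safety.
- Improvements are taken from Sample size calculation: 4.0 − 1.6 = 2.4 for Seeking Safety and 4.0 − 2.8 = 1.2 for CBT. Smaller Seeking Safety improvements of 1.8 and 1.3 are assumed in addition.
- Caution on scale: Instruments and outcome makes the EuropASI composite score the primary outcome, and the EuropASI section gives that score a range of 0 to 1. Improvements of 2.4 and 1.2 cannot occur on it. The numbers therefore show how the quantities behave and do not forecast this trial's ICER. Changing the effect scale would rescale the ICER and leave the defined quantity untouched.

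| Cost SS, CBT | Improvement SS, CBT | Effect difference | As defined | ICER |
|---|---|---|---|---|
| 1200, 1000 | 2.4, 1.2 | 1.2 | 200 | 200/1.2 = 166.7 |
| 1200, 1000 | 1.8, 1.2 | 0.6 | 200 | 200/0.6 = 333.3 |
| 1200, 1000 | 1.3, 1.2 | 0.1 | 200 | 200/0.1 = 2000 |
| 1050, 1000 | 2.4, 1.2 | 1.2 | 50 | 50/1.2 = 41.7 |
| 1050, 1000 | 1.8, 1.2 | 0.6 | 50 | 50/0.6 = 83.3 |
| 1050, 1000 | 1.3, 1.2 | 0.1 | 50 | 50/0.1 = 500 |
| 1000, 1000 | any of the above | 1.2 to 0.1 | 0 | 0 |

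If Seeking Safety did slightly worse (an effect difference of −0.1) at costs of 1200 and 1000, the defined quantity would still be 200, although Seeking Safety would then cost more and achieve less. At equal costs the two quantities coincide at 0, so that case does not show the problem.

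**Does the simple ratio repair it?** At costs of 1200 and 1000 and improvements of 2.4 and 1.2, the per-arm ratios are 1200/2.4 = 500 and 1000/1.2 = 833.3, a difference of −333.3. The ICER is +166.7. The per-arm ratios make Seeking Safety look cheaper per point, while each additional point gained over CBT in fact costs 166.7 units. The two answer different questions, and one cannot stand in for the other.

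**The case against.** The strongest reply is that this is a slip of drafting. The article calls the quantity a ratio, says costs will be related to benefits, names an effect measure, and divides cost by effect in the same paragraph. A ratio consisting of a single difference contradicts itself, so a clause about the difference in effect has probably been lost. This is a plausible account of the intention, but it does not supply the missing denominator.

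Second, the economic aim does not rest on this sentence alone, because cost per QALY gained is also planned. That stands, and it limits the consequence. The QALY sentence does refer to the cost of each strategy without spelling out an incremental comparison, so it would benefit from the same clarification.

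Third, nothing in randomisation, data collection, sample size or the primary test depends on this definition. That also stands.

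A reader might go further in three ways that the documents do not support.

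- One might infer that the cost difference is almost fixed by design, because Study design says "This design keeps dosage equivalent across the treatment conditions". That sentence concerns the number and length of sessions, not cost. The Intervention section describes training, video review and supervision for Seeking Safety that the Comparison condition section does not mention for CBT, and no costs are given.
- One might infer that an unsuitable confidence interval will be used for the ratio. The article names no method.
- One might infer that costs must be widened to service use. The article states a staff-and-materials perspective, and it does not say that the patient file holds service-use data in usable form.

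**Conclusion.** The definition is wrong as written and should be fixed. Read literally, it yields a quantity that carries no information on effect. In the illustration it stays at 200 while the ICER ranges from 166.7 to 2000, and it would still be 200 if Seeking Safety were the worse treatment. These numbers rest on assumed costs and on the severity scale of the sample size section; the conclusion itself follows from the definition and needs neither.

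The reach is limited to one statistic of the second aim. A reader might conclude that the whole economic aim would be answered with the wrong quantity. That is too strong, since the surrounding text points to a lost clause and a cost-per-QALY analysis stands beside it. The primary comparison is not affected.

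**What to change.** Replace the definition with: ICER = (mean cost Seeking Safety − mean cost CBT) / (mean effect Seeking Safety − mean effect CBT). State that effect means improvement on the primary outcome, so that higher is better; the EuropASI score itself measures severity, and without this the sign is ambiguous. Use the same incremental form for cost per QALY gained. State that the comparison between arms rests on the incremental ratio and not on cost divided by effect within each arm.

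This takes a few sentences. It needs no new data, because treatment costs and the primary outcome are already to be obtained. It should be settled before the economic analysis is run, because the quantities above can point in different directions and the choice among them should not follow the results.

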### Data collection

Patients in both treatment conditions will be assessed identically: at the start of treatment (baseline), at the end of treatment (after three months) and at follow up (six months after start of treatment). Patients will be assessed by research assistants at these time points. Under their supervision patients will fill out most of the questionnaires in an online environment in which the data is linked to their electronic patient file.

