### EuroQol-5D (EQ-5D)

For the overall quantification of health status as a single index we will use the standard EQ-5D classification system developed by the EuroQol Group [47]. The EQ-5D is one of the three widely used multi-attribute systems available to determine health state preferences (utilities). The EQ-5D classification describes health status according to five attributes (five questions): mobility, self-care, usual activities, pain/discomfort and anxiety/depression. Each attribute has three levels, i.e., ‘no problems’ (1), ‘some problems’ (2) and ‘severe problems’ (3). Health state descriptions are constructed by taking one level for each attribute (e.g., 11111 represents the highest health status). Theoretically this set of attributes and the levels of the EuroQol-5D instrument allow for 243 (35) different health-status descriptions. Based on the descriptive classification of the EQ-5D system a preference index (utility) can be estimated that expresses the overall preference of the classified health status. These utility figures are required to calculate Quality-Adjusted Life Years (QALYs) for the cost-utility analysis [48].

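### The QALY benefit is defined as baseline minus follow-up, which turns improvement into a loss, and it rests on projecting a six-month utility over life expectancy with no stated persistence assumption

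*Protocol article*

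**What the plan says.** The second aim of the Protocol article is an economic comparison of Seeking Safety with CBT. Within it, the Cost-effectiveness analysis section plans a cost-utility analysis and fixes four things.

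- **Utilities used.** Participants' preferences are taken "considering their own health status at the start of treatment and after follow-up", that is, at two time points.
- **How they become QALYs.** "Based on these preferences combined with life expectancy figures, calculation of so-called QALYs is applicable".
- **Benefit.** The measure of what each arm achieves is to be obtained "by subtracting the number of quality-adjusted life years computed after follow-up from the number of QALYs computed at baseline".
- **Use.** Afterwards, "quality-adjusted life years can be combined with the cost of each treatment strategy to arrive at the cost per QALY gained". The costs that the section names are those of the treatments themselves, for staff and materials.

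The EuroQol-5D section supplies the utilities and gives the direction of the health description: "11111 represents the highest health status". It gives no schedule for the instrument. The Data collection section sets the assessments "at the start of treatment (baseline), at the end of treatment (after three months) and at follow up (six months after start of treatment"), and the abstract likewise has questionnaires administered at all three points.

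**The concern.** Two features of the stated method do not fit its purpose.

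First, subtracting the follow-up value from the baseline value gives baseline minus follow-up. Better health should raise the utility and hence the QALYs, so improvement comes out negative. Anyone who programs the rule as written would report the more effective arm as the less beneficial one.

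Second, no time has elapsed at baseline, so a number of QALYs computed then makes sense only as a projection over remaining life. The same holds for the value after follow-up. The benefit therefore carries a utility seen at six months across decades that were not observed, and sets it against the cost of a 12-session programme. The Implications for practice section intends these results for policy makers, who would read the cost per QALY at face value.

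**Working it through.** The document gives no QALY, utility or life-expectancy figure, so there is no stated result to reproduce. The check is algebra from the stated rule, with assumed inputs marked as such.

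**Notation.** u0 and u2 are the utilities at t = 0 and t = 2, d = u2 − u0 is the gain, and L is remaining life expectancy in years (not given; assumed 10 to 50). The plainest reading of combining a preference with life expectancy is utility × L.

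**Step 1: sign.**
Benefit as written = u0·L − u2·L = −L·d, which is negative whenever d > 0.
- Assumed utilities 0.60 and 0.70, L = 40: 0.60 × 40 − 0.70 × 40 = 24 − 28 = −4.0. In the right order it is +4.0.
- Two arms, assumed gains 0.10 (Seeking Safety) and 0.05 (CBT), L = 40: −4.0 against −2.0. The difference, Seeking Safety minus CBT, is −2.0, so the better arm ranks lower.

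The reversal does not depend on L or on the lifetime horizon. It occurs for any QALY measure that rises with health.

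**Step 2: size of the lifetime projection.**
In the right order, the lifetime gain is L·d. QALYs gained over the observed half year depend on how fast the gain appears:
- linear from 0 to 6 months (two readings): 0.5 × d/2 = 0.25d
- full gain by month 3, then held (three readings): 0.25 × d/2 + 0.25 × d = 0.375d
- full gain from the first day (upper limit): 0.5d

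The gain d cancels, so the ratio of lifetime to within-trial QALYs is L/0.25, L/0.375 or L/0.5:

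| Assumed L (years) | Linear | Full by month 3 | Full from day 0 |
|---|---|---|---|
| 10 | 40 | 27 | 20 |
| 20 | 80 | 53 | 40 |
| 30 | 120 | 80 | 60 |
| 40 | 160 | 107 | 80 |
| 50 | 200 | 133 | 100 |

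The undiscounted range is about 20 to 200. With assumed annual discounting at rate r, L is replaced by (1 − (1 + r)^−L)/ln(1 + r). For L = 40 and r from 1.5% to 4%, the ratio falls to about 121 to 81 (linear) or 60 to 40 (full from day 0).

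**Step 3: when this is overstatement.**
Suppose the full gain is present from day 0, lasts P years and is then lost. The true QALY gain is P·d and the projection exceeds it by L/P. For L = 40: P = 0.5 gives 80, P = 10 gives 4, and P = 40 gives 1. With cost held fixed, cost per QALY is too low by the same L/P. The large factors in the table therefore apply in full only if nothing of the gain survives month 6.

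**The case against.** The reversed order is probably a slip of wording. The section calls the quantity a measure of benefits and goes on to a cost per QALY gained, so the intended direction is clear and a reversed published result is unlikely. That is fair as to intent. It remains the only definition of benefit given for the cost-utility analysis, and it is wrong as it stands.

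A horizon beyond follow-up is a legitimate modelling choice, and an article may leave persistence, discounting and valuation to a fuller document. This also stands, and the absence of a discount rate is not the point. The point is that the article makes the projection its only QALY calculation and does not mark it as extrapolation.

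A reader might infer stronger claims that the document does not support:

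- *That QALYs are inflated about 100-fold.* A factor of 100 needs an L of 25, 37.5 or 50 years, depending on the within-trial comparator. No life expectancy or mean age is given, and the factor shrinks if the gain lasts.
- *That an end-of-treatment EQ-5D is collected and then ignored.* Collection at t = 1 is likely from the abstract and the Data collection section, but nothing states it for this instrument. What is stated is that the QALYs use two readings.
- *That the analysis is purely pre-post within each arm.* The section opens by comparing the two treatments and names an incremental ratio as the statistic of interest. Its wording for that ratio mentions only a cost difference, however, so the QALY denominator still needs to be written down.
- *That utility is certainly multiplied as a constant by L.* The text says only that the two are combined. Constant multiplication is the natural reading, not a quotation.

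**Conclusion.** The point holds in two parts. The sign error is certain from the text: improvement is recorded as a loss, the arms are ranked in reverse, and the section contradicts itself. The reliance on life expectancy is also in the text. With two readings and six months of follow-up, it yields a benefit that is almost wholly extrapolated, has no stated persistence assumption, and is matched to short-term treatment costs only.

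The size of any overstatement cannot be fixed from the document. Roughly 20- to 200-fold relative to within-trial QALYs is an illustrative range. It assumes 10 to 50 years of remaining life, no discounting and a constant projected utility, and it counts as overstatement only so far as the gain fades. The consequence is confined to the cost-utility part of the second aim. The primary outcome, the sample size and the efficacy comparison are not touched.

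**What to change.** 1. Correct the order: QALYs after follow-up minus QALYs at baseline, wherever a change is reported.
2. Make the main cost-utility analysis within-trial. For each patient, compute QALYs over six months as the area under the EQ-5D utility curve through t = 0, t = 1 (if the EQ-5D is collected then, which should be stated) and t = 2.
3. State the denominator of the incremental cost per QALY: the Seeking Safety minus CBT difference in these QALYs, adjusted for baseline utility. The numerator is the difference in cost over the same six months.
4. Report any lifetime extrapolation as a labelled scenario, with its persistence and discounting assumptions written out and varied.

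Items 2 to 4 go beyond repairing the sign. They are the simplest way to keep the main result within what the trial observes. The cost is rewording and a simpler calculation on data that the trial appears to collect already. The downside is a smaller QALY difference and a less favourable cost per QALY.
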